### Process evaluation

An evaluation questionnaire will be administered to those participants in the Group CBT intervention arm at the end of the six-week intervention. Interviews will be conducted with patients and key stakeholders from each of the study centres at the completion of the intervention. Semi-structured interview schedules will be developed, guided by consideration of the four areas identified through NPT [33], which includes an exploration of barriers to implementation and how they were tackled. Key stakeholders will include all the participating BCNs and 1 key manager and 1 key member of clinical staff at each site identified by the BCNs. Interviews will be conducted with BCNs prior to, and after delivery of the intervention. All other stakeholders will be interviewed after the intervention. Interviews will be either face-to-face or by telephone.

### Analysis

#### Sample size calculation

A difference of two points or more in the HFNS Problem Rating Scale is regarded as clinically relevant. In order to detect a two-point difference (standard deviation 2.4; standardised effect size 0.8, [26] in mean HFNS problem rating for the comparison of CBT to TAU, 90% power would require 64 participants in total (32 per randomised arm), assuming 2-sided significance level of 0.05. Allowing for an inflation factor of 1.49 (intraclass correlation of 0.07 with 8 participants per group, (Wampold and Brown [36]) to adjust for expected clustering of outcomes within groups, gives a minimum sample size of 96, which increases to 120 allowing for 20% loss to follow-up. A sample size of 120 will also allow each site to run two groups to ensure that a comprehensive process evaluation can be conducted. If each site recruits the minimum number of six people per group, then 120 participants in total will be achieved. If they recruit the maximum of eight per group (allowing up to 160 participants in total) this will provide greater power for the analyses of secondary outcomes.

#### Primary and secondary analyses

Scales from the validated questionnaire measures will be calculated according to published scoring algorithms. The difference in the HFNS Problem Rating Scale (primary outcome) between the two randomised groups will be tested using a linear mixed model, utilising fixed and random effects. The regression model will compare the HFNS problem rating subscale between intervention groups at follow-up, adjusting for baseline HFNS problem rating score and stratification factor (site). Greater precision of estimates is expected within therapy groups (clustering effect) so models will also be adjusted for the group. Secondary outcomes at post-treatment will be analysed in a similar way. Follow-up data at subsequent time intervals will also be explored through linear mixed models utilising repeated measures analyses, allowing simultaneous modelling of the three outcome time points. Analyses will be based on a modified intention-to-treat sample (i.e. excluding participants who contribute fewer than two items on the primary outcome measure). Per protocol analysis for those compliant will be performed as a sensitivity analysis.

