### Intervention

Women in the intervention arm will attend weekly group CBT sessions, lasting 90 min each, for six weeks. Sessions will be delivered by BCNs who have been trained by a clinical psychologist. The sessions will follow a structured manual [20], which includes psycho-education and the cognitive behavioural model; stress management; paced breathing; cognitive and behavioural strategies to improve wellbeing and for managing hot flushes; night sweats and sleep; and maintaining changes.

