### Adherence

Adherence to group CBT will be measured by the number of sessions attended and the number of times that a participant reports practising relaxation and paced breathing each week. If participants do not attend a session, the BCN will contact the participant by telephone to ascertain the problem of attendance, and will discuss the appropriate solution with the participant e.g. a telephone session. Alternatively, the session is recorded as did not attend. Telephone sessions will be kept to a minimum, and only arranged if exceptional circumstances do not allow the patient to attend the face-to-face session.

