### Treatment as usual arm

It is expected that TAU will be different at each site as there is no current standard of care. Since randomisation will be stratified by site this does not pose a problem. In some centres, women will be given ad hoc advice about HFNS, normally only if they raise the issue. Data collected from a UK survey suggests that only 29% women were asked if they were experiencing HFNS, only 2% were referred to a menopause clinic and very few offered any kind of relaxation or behavioural intervention [15].

In addition to standard NHS care, participants randomised to the TAU arm will be offered a version of self-help CBT following the 26-week assessment. This involves giving women a booklet and CD that includes the same information as group CBT sessions, as well as a one-to-one face-to-face meeting with a trained BCN to discuss the key elements of the booklet. This will be followed up by two telephone calls to discuss progress, encourage use of the booklet and homework and to address any problems. Offering self-help CBT will be used as a strategy to increase adherence to the study.

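### The per-protocol sensitivity analysis selects on attendance that is measured only in the CBT arm, so it does not test the robustness of the modified intention-to-treat result; a supplementary complier-average causal effect (CACE) would serve better

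*Protocol article*

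**What the plan says.** All references are to the protocol article.

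- *Primary and secondary analyses* sets the main analysis set: "Analyses will be based on a modified intention-to-treat sample (i.e. excluding participants who contribute fewer than two items on the primary outcome measure". It then adds: "Per protocol analysis for those compliant will be performed as a sensitivity analysis". The article gives no compliance cut-off and does not say which TAU women enter this set.
- *Adherence* gives the only compliance measure: "Adherence to group CBT will be measured by the number of sessions attended and the number of times that a participant reports practising relaxation", together with paced breathing. A missed session leads to a call and possibly a telephone session; "Alternatively, the session is recorded as did not attend".
- *Intervention* gives the intended exposure: "Women in the intervention arm will attend weekly group CBT sessions, lasting 90 min each, for six weeks".
- *Treatment as usual arm* rules out planned access to CBT before the primary endpoint: "participants randomised to the TAU arm will be offered a version of self-help CBT following the 26-week assessment".
- *Study aims and objectives* places the primary endpoint at 26 weeks after randomisation.

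**The concern.** Attendance happens after randomisation and is observed only among women offered the groups. Restricting to compliers can remove women from the CBT arm who did not attend, but their counterparts in TAU cannot be identified. If women who attend differ in prognosis from women who do not, the contrast mixes that difference with the effect of CBT.

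The label matters as well. A sensitivity analysis should vary the assumptions behind one estimate. This one moves to a different quantity and adds confounding, so neither agreement nor disagreement with the modified intention-to-treat result says much about how robust that result is. At stake is how the effect of actually receiving nurse-led CBT is reported, not the primary test.

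**Working it through.** **Plan's own figures.** The article states no figure for this analysis, so only its sample size serves as input. With a 2-point difference, SD 2.4, two-sided 5% and 90% power, the t-based calculation gives 31.3, so 32 per arm or 64 in total. The design effect is 1 + (8 − 1) × 0.07 = 1.49; 64 × 1.49 = 95.4, taken as 96; 96 / 0.80 = 120. These reproduce the *Sample size calculation* section. I use 96 / 2 = 48 analysed women per arm.

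**Assumed, because the article does not give them.** Share compliant p = 0.6 to 0.9. Would-be non-attenders score delta = 0 to 1.5 points worse than attenders under TAU, after adjustment for baseline score and site. True effect is −2 in compliers and 0 in others (lower scores are better). The per-protocol contrast is taken as compliant CBT women against all TAU women.

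**Per protocol.** Let m be the attenders' mean under TAU.

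- Compliant CBT mean = m − 2.
- TAU mean = p × m + (1 − p) × (m + delta) = m + (1 − p) × delta.
- Difference = −2 − (1 − p) × delta, so the bias is −(1 − p) × delta.

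| p | delta 0 | delta 0.5 | delta 1.0 | delta 1.5 |
|---|---|---|---|---|
| 0.9 | 0 | −0.05 | −0.10 | −0.15 |
| 0.8 | 0 | −0.10 | −0.20 | −0.30 |
| 0.7 | 0 | −0.15 | −0.30 | −0.45 |
| 0.6 | 0 | −0.20 | −0.40 | −0.60 |

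The largest value, 0.60, is 30% of the 2-point target. The true effect does not enter the bias, so at p = 0.7 and delta = 1 a treatment with no effect would show −0.30.

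**CACE.** The intention-to-treat effect is −2 × p, and CACE divides it by p. At p = 0.7: −1.40 / 0.7 = −2.00. A 4,000-run simulation at p = 0.7 and delta = 1, without clustering, gave −2.30 for per protocol and −1.99 for CACE.

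**Precision at p = 0.7**, with the design effect applied in the CBT arm only:

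- Intention to treat: 2.4 × √(1.49/48 + 1/48) = 0.55.
- Per protocol: 2.4 × √(1.49/33.6 + 1/48) = 0.61, where 33.6 = 48 × 0.7.
- CACE: 2.4 × √(1.49/48 + 1/48) / 0.7 = 0.78.

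**When CACE fails.** Suppose 70% comply, and a further 20% attend below the cut-off but gain 1 point. Intention to treat = −(0.7 × 2 + 0.2 × 1) = −1.60, and CACE = −1.60 / 0.7 = −2.29 instead of −2.00. That error is about the size of the per-protocol bias at p = 0.7 and delta = 1.

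**The case against.** **The comparison with all TAU women is inferred.** The article does not define the TAU part of the set, and the full protocol or analysis plan may do so. TAU women could also be counted non-compliant, since *Participants* asks women already using HFNS medication or herbal remedies to continue them and excludes current users of other mind-body therapies. This stands as a limit on the wording. It does not remove the fault: no TAU rule can identify women who would not have attended a group they were never offered.

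**Size and direction are assumed.** This stands. The model adjusts for baseline score and site, so only the residual gap counts, and 1.5 points is 0.63 of the SD (1.5 / 2.4). Being able to attend groups is an entry criterion and missed sessions are followed up, which favours high compliance; at p = 0.9 the bias is at most 0.15. If more troubled women attend more, the sign reverses. A reader might infer that per protocol will exaggerate the benefit or rescue a weak primary result. The article supports neither.

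**CACE is not plainly more accurate.** At p = 0.7 and delta = 1.5 the root mean square error of per protocol is √(0.61² + 0.45²) = 0.76, against 0.78 for an unbiased CACE. This stands. The gain is in validity: the CACE numerator is the randomised contrast, so selection on attendance cannot create an effect where there is none.

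**CACE has its own target and assumptions.** This also stands. It would be wrong to say that it answers the same question without bias.

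**Conclusion.** The concern holds in a limited form. The article commits to an analysis that, on the natural reading, selects on post-randomisation attendance in one arm, and it calls this a sensitivity analysis. It loses the protection of randomisation and does not test the modified intention-to-treat estimate. The possible bias is 0 to 0.6 points over the assumed ranges, and nothing in the document narrows that range or fixes its sign.

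A reader might go further and doubt the main result, or the two-point criterion that triggers the economic evaluation. The documents do not support that: the main analysis is modified intention to treat, and neither the primary conclusion nor the economic trigger is tied to the per-protocol analysis. The point is worth correcting but does not block the trial.

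**What to change.** Report a CACE estimate of the 26-week problem rating, in place of or beside per protocol, and label it a supplementary estimand.

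- Use randomised arm as the instrument for attendance, by two-stage least squares or an equivalent method, adjusted for baseline score and site.
- Define attendance before outcome data are seen, including how telephone sessions count.
- Handle clustering by therapy group with a method suited to about 12 groups (six sites, two groups each), all in one arm; ordinary cluster-robust errors are doubtful with so few.
- State that the estimate applies to women who would comply if offered CBT, and that it assumes allocation has no effect on women classed as non-attenders. That is doubtful if partial attenders benefit. A version using the number of sessions relaxes this only by assuming a linear dose effect.
- If per protocol is kept, call it descriptive and state which TAU women it includes.

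The data needed are already planned: arm, attendance and the week-26 outcome. TAU women have no planned access to CBT before then, so non-compliance is one-sided by design. The sample size does not change. The costs are some analysis work, a wider interval than per protocol (standard error about 0.78 against 0.61 at 70% compliance) and an assumption that must be defended. Missing 26-week outcomes still need separate handling.

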#### Health economics analysis

All relevant resource items identified will be costed using published national cost data (British National Formulary and Personal Social Services Research Unit, and NHS reference cost). Accumulated costs and quality adjusted life years (QALYs) per patient will be estimated by means of area under the curve. Where appropriate we will estimate incremental cost-effectiveness ratios. We will estimate mean values and 95% percentiles using non-parametric bootstrapping. We will produce cost-effectiveness acceptability curves to illustrate the uncertainty of such estimates. Major assumptions made in the costing and QALYs will be tested by means of sensitivity analyses.

#### Qualitative analysis of process evaluation

Interview recordings will be transcribed and all identifying data will be anonymised. The data will be analysed using thematic analysis [5] and the principles of open coding, constant comparison, negative case analysis, and memo writing [27]. In addition, some a-priori codes derived from the literature review will be used. The NVivo 10 software program will be used to facilitate data storage, categorisation and retrieval. Members of the research team will code the interviews, hold coding meetings, and revise the coding strategy. After coding, themes will be proposed and tested in the data. Analysis meetings with the research team will involve refining the themes.

Fidelity of delivery of the therapy will be assessed from randomly selected audio recordings. An experienced, independent clinical psychologist will indicate on coding sheets the extent to which the group leader covered each topic, using the Quality Assurance for Group CBT intervention Independent Sessional Assessment tool used in MENOS study 1 [26]. Coding sheets include specific components of the intervention (e.g. reviewing homework, providing information about the role of stress, demonstrating paced breathing in the session, group discussion of behaviours relating to HFNS) developed for the trial.

## Discussion

There is a need for studies that enable effective interventions to be implemented in practice. There is good evidence that CBT is helpful for women with breast cancer [26], yet it is not widely available. It is not yet known whether the intervention can be effectively delivered by BCNs. This study will provide information on both whether the intervention can effectively help women with HFNS and whether and how it can be translated into routine clinical practice.

Despite the fact that CBT has been demonstrated to be effective in relieving the bother of HFNS in women who have had breast cancer, it is not widely available and is rarely offered to women who are suffering these symptoms. One reason for this could be the relatively small number of therapists available to offer this kind of intervention. Most women with breast cancer have access to a BCN and nurses can be effectively trained to deliver psychological interventions. If it can be shown that this intervention can be successfully delivered by BCNs this could make the intervention available more widely. However, there are often other barriers to the implementation of effective therapies, so this study will provide a qualitative evaluation of challenges and barriers and how participating centres overcame these to implement this service into their practice (Figs. 1, 2 and Additional file 1).

**Fig. 1 Fig1:**
[figure not shown]
Schedule of observations and procedures

**Fig. 2 Fig2:**
[figure not shown]
Study Schema

### End of the trial

The end of trial is defined as when the last patient has had their last data collected.

### Trial status

This clinical trial was registered in January 2017 (ISRCTN (12824632)). Recruitment opened in January 2017 and is expected to be completed by March 2018. The current protocol is version 3, dated 21-April-2017. Results will be published at the end of the trial in a peer reviewed journal (authored by the members of the TMG), presented at international conferences, end of trial summaries will appear on the relevant databases and results fed back to recruiting sites so that any participants are able to access the results via their treating clinician.

### Oversight groups and committees

The trial is overseen by the TSC. No DMEC will be convened; this role will be assumed by the TSC.

## Abbreviations

BCN: Breast Care Nurse
CBT: Cognitive Behavioural Therapy
CEAC: Cost-Effectiveness Acceptability Curves
CRF: Case Report Form
CSRI: Client Service Receipt Inventory
DCIS: Ductal Carcinoma in Situ
DMEC: Data Monitoring and Ethics Committee
EQ-5D-5 L: European Quality of Life-5 Dimensions-5 Levels
FACT-B: Functional Assessment of Cancer Therapy for Patients with Breast Cancer
FACT-ES: Functional Assessment of Cancer Therapy for Patients with Endocrine Symptoms
GAD-7: Generalised Anxiety Disorder Questionnaire
GCP: Good Clinical Practice
HFBBS: Hot Flush Beliefs and Behaviour Scale
HFNS: Hot Flush and Night Sweats
HFRDIS: Hot Flash Related Daily Interference Scale
HRT: Hormone Replacement Therapy
ICER: Incremental Cost-Effectiveness Ratios
ISF: Investigator Site File
NCRI: National Cancer Research Institute
PHQ9: Patient Health Questionnaire-9
PI: Principal Investigator
PIS: Participant Information Sheet
PSQI: Pittsburgh Sleep Quality Index
QALY: Quality Adjusted Life Years
QoL: Quality of Life
RCT: Randomised Controlled Trial
REC: Research Ethics Committee
RN: Research Nurse
SAE: Serious Adverse Event
SCTU: Southampton Clinical Trials Unit
SSRI: Selective Serotonin Re-uptake Inhibitors
SUSAR: Suspected Unexpected Serious Adverse Reaction
TM: Trial Manager
TMF: Trial Master File
TMG: Trial Management Group
TSC: Trial Steering Committee
